### Monitoring

#### Data monitoring and ethics oversight

This feasibility trial is expected to pose minimal risk to participants, and hence no formal data monitoring committee has been established. However, the research team will produce regular data monitoring reports for the project steering group, composed of a trial statistician, clinician and public involvement member, who are independent of the project management team and will assess and monitor the data quality on an annual basis throughout the study.

#### Harms

MRI scanning is non-invasive and has no known significant adverse health effects when appropriate screening and safety measures are in place and implemented. CUBRIC SOPs will be followed to ensure this. Any adverse effects including rare events of peripheral nerve stimulation, dizziness, mild nausea during the MRI scanning will be monitored, recorded and documented. These side effects, if experienced, may be uncomfortable but resolve after leaving the magnetic field and participants will be warned at the beginning of the scanning session. It will also be explained that the researchers do not have expertise in MRI diagnosis, as they are not medical doctors. Participants should not regard the research scans as medical screening procedures and if they had any health concerns, they should contact their general practitioner (GP). In the unlikely event of an unexpected finding, a neurological consultant [name] will be asked to examine the scans, and if appropriate to report back to the participant’s GP.

Finally, in the unlikely event of adverse events occurring from the HD-DRUM intervention or the cognitive and motor assessments, these will be monitored, recorded and reported.

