**Figure 2 F2:**
[figure not shown]
The HD-DRUM app environment. (A) The app home screen interface that allows users to navigate through and select unlocked training sessions. (B) The virtual drums, a blue triangle (high pitch bongo) and red circle (low-pitch bongo), participants use to tap in synchronisation with the audio instructions.

Participants in the intervention group will be provided with a tablet with the HD-DRUM app installed and an instruction manual for home use. Following completion of baseline assessments participants will receive a face-to-face introduction to the app to familiarise themselves with HD-DRUM. To support retention of the intervention, researchers will maintain weekly contact with participants to provide feedback, assist with any queries or problems and help remove potential barriers. Whenever possible, family members and/or carers will be encouraged to support engagement with the training. Participants will report what support they found helpful in an intervention evaluation questionnaire. Participants in the control condition will be offered the opportunity to borrow a tablet with HD-DRUM to try the training out after they have completed the final assessment of the study.

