##### Secondary outcome measures

Performance in the following measures will be assessed before and after 8 weeks of intervention or usual-activity control (see table 1 for participant timeline).

**Table 1 T1:** Schematic diagram of participant timeline

Assessments for all participants			
	Baseline study visit	HD-DRUM training intervention (completed at home with support and reminders) or control time period	Follow-up study visit
	Day 1	8-week intervention period	End of week 8 (+ 2 weeks)
Cohort Descriptive information			
MOCA*	X		
TOPF	X		
Self-report questionnaire			
Patient Health Questionnaire-8	X		X
HD-DRUM participant evaluation survey			X
Paper and pencil tasks			
Stroop task	X		X
Verbal fluency	X		X
SDMT	X		X
Categorical fluency	X		X
Verbal trails (letter-digit switching)	X		X
Computerised tasks			
N-back Audio (letters)	X		X
N-back Visuospatial (square changing positions in grid)	X		X
N-back dual (audio and visuospatial)	X		X
Flanker task	X		X
Q-Motor assessments			
Speeded finger tapping (left/right index finger)	X		X
Finger metronome tapping (left/right index finger)	X		X
Pointing and tapping (dominant hand)	X		X
Dual (pointing and tapping with dominant hand, speeded finger tapping with opposite hand)	X		X
Speeded foot tapping (left/right)	X		X
Metronome foot tapping (left/right)	X		X
Brain imaging			
T1-weighted MPRAGE	X		X
msHARDI	X		X
qMT	X		X
mcDESPOT	X		X
HD-DRUM group			
HD-DRUM training intervention supported by email and telephone reminders		X	
Control group			
Standard care, usual activities		X	

HD, Huntington’s disease; mcDESPOT, multicomponent-driven equilibrium single pulse observation of T1 and T2; MOCA, Montreal Cognitive Assessment; msHARDI, multi-shell high angular resolution diffusion imaging; qMT, quantitative magnetisation transfer; SDMT, Symbol Digit Modalities Test; T1-MPRAGE, T1-weighted Magnetisation Prepared-Rapid Gradient Echo Sequence; TOPF, test of premorbid functioning

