#### Blinding (masking)

The researchers conducting the baseline assessments (cognitive, motor and MRI) have no access to the randomisation list implemented in REDCap and will be blind to the group allocation until baseline assessments are completed. However, once group allocation has taken place at the end of the baseline assessments, blinding of the researchers involved in the data collection and participants will not be possible due to the nature of the intervention and control conditions and due to limited resources and staffing. The analysis of the Q-Motor data will be conducted blind to group allocation by an independent researcher not involved in the data collection [name]. The lack of blinding of the clinical and MRI outcomes is a limitation of the study design, but quantitative outcome measures have been used where possible to minimise any potential biases that may be introduced due to a lack of blinding.

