### Data collection, management and analysis

#### Data collection methods

The project will be conducted following Good Clinical Practice, data protection in accordance with the Data Protection Act 2018, and CUBRIC standard operating procedures (SOPs) including MRI safety and operation guidelines. The project will adhere to any applicable Centre for Trials Research SOPs, including those for project management, data management and protection, and adverse/serious adverse event reporting. Research staff will receive training in the above.

Training-specific performance improvements, namely speed and accuracy of drumming, will be recorded by the HD-DRUM app. Frequency and duration of training engagement will also be recorded by HD-DRUM as a measure of adherence.

Cognitive and motor performance measures will be collected on paper data collection forms and electronically via PEBL and MATLAB on a personal computer in a quiet testing room in CUBRIC. Electronic data capture of Q-Motor data are automated by the Q-Motor data acquisition software Q-MedX.

MRI data will be acquired on the 3 Tesla MRI Siemens Connectom system at CUBRIC.

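### Outside MRI, the Harms section makes attribution the condition for recording an adverse event, so events during the 8 weeks at home cannot be compared between arms as worded

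*Protocol article*

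**What the plan says.** The Harms section sets two recording rules. For scanning: "Any adverse effects including rare events of peripheral nerve stimulation, dizziness, mild nausea during the MRI scanning will be monitored, recorded and documented". For everything else, the commitment is to "adverse events occurring from the HD-DRUM intervention or the cognitive and motor assessments, these will be monitored, recorded and reported".

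On who would attribute events, the Blinding section says that after allocation "blinding of the researchers involved in the data collection and participants will not be possible".

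On contact between visits, the Intervention section (text following Figure 2) says: "To support retention of the intervention, researchers will maintain weekly contact with participants to provide feedback, assist with any queries or problems". Table 1 lists, for the HD-DRUM group, "HD-DRUM training intervention supported by email and telephone reminders" and, for the control group, only "Standard care, usual activities".

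The Data collection methods section adds that the project will follow any applicable trials-unit operating procedures, "including those for project management, data management and protection, and adverse/serious adverse event reporting". Their content is not shown.

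**The concern.** The non-MRI rule puts the causal judgement before the record. In a progressive disease that order matters. A fall, hand pain or fatigue (my examples) over 8 weeks could come from the disease, the training or neither, and it is the randomised control arm that allows these to be separated. If an event is written down only once someone who knows the allocation has tied it to the app or the tests, the control arm has nothing to offer for the home period.

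Unequal contact adds to this. A problem mentioned at a weekly call in the HD-DRUM arm has a route to the study team that a control participant's problem is not described as having.

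The trial is meant to decide whether and how to run a larger effectiveness trial, so its harms procedure may well be carried forward.

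**Working it through.** The protocol gives no adverse event figure to reproduce. Its only precision statement, ±15 percentage points for feasibility rates with 50 participants, is correct (largest one-sided distance 13.9 points by Wald, 14.8 by Clopper-Pearson). This point does not depend on it. The main check is of the wording.

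**1. What can be recorded in each arm**

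| Source of event | HD-DRUM arm | Control arm |
|---|---|---|
| MRI session | any adverse effect during the scan | same |
| Cognitive and motor testing | if attributed to the testing | same |
| 8 weeks at home | if attributed to HD-DRUM | no event can qualify |

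The MRI rule depends on when the event happens and applies to everyone scanned. The home-period rule depends on cause, and only one arm is exposed to that cause. The control arm is therefore not empty overall, because scan and assessment events can be recorded there. It is empty for the home period.

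**2. Who attributes.** From allocation onwards, the researchers collecting data know the arm. Blinded analysis is described only for the Q-Motor data, which does not help with adverse events.

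**3. Opportunity to hear of events.** Both arms attend baseline and follow-up. Between visits, contact is described only as support for the training, and Table 1 lists none for controls.

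**4. What is compared fairly.** Q-Motor, the cognitive battery and the Patient Health Questionnaire-8 are taken at both visits in both arms (Table 1). The Statistical methods section summarises change by group. It also notes that no change relative to controls may point to benefit because the disease progresses. The same reasoning applies to harms, but the recording rule does not allow it for discrete events.

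**5. Why widening the scope alone is not enough.** Suppose all events counted, the true risk p were equal in both arms, the HD-DRUM arm captured every event and controls captured a fraction c. The apparent excess is p − p × c = p × (1 − c). All values of p and c are assumptions.

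| True risk p | c = 0 | c = 0.5 | c = 0.8 |
|---|---|---|---|
| 10% | 10 points | 5 points | 2 points |
| 20% | 20 points | 10 points | 4 points |
| 30% | 30 points | 15 points | 6 points |

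These figures describe no analysis in the plan. They show why the method of asking must be the same in both arms.

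**6. What a fair comparison could deliver.** Assume 25 per arm (50 participants, 1:1; no ratio is stated). The 95% half-width is 1.96 × √[p₁(1 − p₁)/25 + p₂(1 − p₂)/25]:

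- 10% v 20%: 1.96 × √(0.09/25 + 0.16/25) = 19.6 points
- 10% v 30%: 1.96 × √(0.09/25 + 0.21/25) = 21.5 points
- 20% v 40%: 1.96 × √(0.16/25 + 0.24/25) = 24.8 points

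**The case against.** The strongest reply is that the Harms text is a short summary in a condensed article. It does not say that other events go unrecorded, and the project follows adverse event procedures that may be wider. Definitions and relatedness fields are commonly left to such documents. This stands in part: nobody reading the article can say that the procedures share the narrow scope. But the article does state a causal scope. If the procedures are wider, the two texts need reconciling; if they are not, the gap is real.

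Second, a reader might infer that the control arm cannot show whether HD-DRUM causes harm, or that harm resembling the disease would be recorded in neither arm. The protocol does not support either reading. Worsening of movement, cognition or mood is measured alike in both arms and compared. What those measures miss is discrete events outside their domains, and events in people who do not return for follow-up.

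Third, the weekly contact is there to support training; it is not described as adverse event questioning. No passage says that controls are never contacted. Both are correct. The imbalance is an inference from the Intervention section and Table 1, though a sound one.

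Fourth, the trial is described as minimal risk, has no harms objective and plans no between-arm adverse event table. Intervention participants are also asked about detrimental training effects in the acceptability questionnaire. This limits the weight of the point. However, that question too asks for effects already attributed to training, so it gives no control rate.

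**Conclusion.** The point holds in limited form. Outside MRI, the stated rule requires attribution before recording, attribution is unblinded, and described between-visit contact is one-sided. Following the text gives no comparable control count of discrete adverse events in the home period. The conclusion stops there: it does not extend to group-level motor, cognitive or mood change, to MRI or assessment events, or to the content of the unseen procedures.

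No figure in the protocol changes. The size of any bias cannot be derived from the documents, and a reader should not infer a particular inflation of the harm rate: the risks and capture fractions above are assumptions. With about 25 per arm, any harms comparison would remain descriptive, with half-widths of roughly 20 to 25 points. That imprecision is no reason to keep a rule that prevents a fair comparison when a better one is cheap. This is a worthwhile improvement, not a flaw that threatens the primary feasibility aim.

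**What to change.** Reword the non-MRI part of the Harms section, and reconcile it with the adverse event procedures cited under Data collection methods, so that:

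- every new or worsened event from baseline to follow-up is recorded in both arms, regardless of suspected cause;
- events are collected with one identical structured question at the follow-up visit that both arms already attend;
- relatedness is recorded afterwards, as a separate field;
- any between-arm harms summary uses only that question, and is labelled descriptive;
- events that came to light only through weekly HD-DRUM contact are listed separately.

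The cost is a wording change, one question and the matching form fields, with no extra visit. More unrelated events will be logged, and assessing relatedness takes some staff time. The question misses anyone who does not attend follow-up. Asking it by telephone would close that gap at some further staff cost, which the team should weigh against the limited staffing noted in the Blinding section.

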## Ethics and dissemination

### Research ethics approval

The study will be conducted in accordance with the recommendations for physicians involved in research on human participants adopted by the 18th World Medical Assembly, Helsinki 1964 and later revisions. Ethical approval for this feasibility study was given by the Wales Research Ethics Committee (REC) 2 (22/WA/0147). Cardiff University has agreed to act as a sponsor for the study (SPON1895-22).

All amendments to the ethical approval will be recorded in the trial registration and any future amendments to be made will be done in accordance with the Integrated Research Application System regulation and will be communicated to sites via the UK permissions system.

### Consent

Informed written consent will be sought by means of participants’ dated signature and dated signature of the person who obtained the informed consent on the consent form provided in online supplemental appendix. The participant will be allowed as much time as needed to consider the PIS and given the opportunity to ask the researcher or independent parties any questions to decide on participation. All participants will have the procedures explained to them in detail, including that the study design is randomised, and be reminded that they can withdraw at any time, without the need to give a reason. The original signed consent form will be retained at the study site in CUBRIC, and participants will receive a copy.

### Access to data

This project has been endorsed by the Enroll-HD Scientific Oversight Committee (SOC) (14/11/2022) and use of Enrol captured data has been approved for this trial. Enrol captured UHDRS data together with volumetric measurements of the caudate and putamen from the T_1_ weighted images acquired in this study, will allow us to report our outcome measures stratified according to the new Huntington’s Disease Integrated Staging System.^44^ ENROLL-HD captured data will also allow us to explore the impact of clinical symptoms including depression and apathy on feasibility. At the end of the project, the coded study data will be shared and made accessible to the research community *via* the Enroll-HD-specific data request process.

### Dissemination policy

Dissemination activities to share the progress and results of our projects with people affected by HD will be led by our PPI contributors. Dissemination strategies will include information sessions for people affected by HD, clinicians, and the general public, as well as communications *via* social media, newsletters and websites of the HDA, the European Huntington Disease Network (EHDN) and HCRW. The findings of this trial will be disseminated as scientific publications and presentations at conferences including at the biennial EHDN plenary meeting. Authorship eligibility will be assessed following the International Committee of Medical Journal Editors guidelines.
